With our study, we aim to fill this gap by applying recent advances in NLP and multimodal methods. Our goal is to help identify non-explicit content language patterns in clinical patients, which can serve as prognostic markers specifically for the German language. Thus, our primary aim is to assess the suicide risk in patients with depression, bipolar disorder, and psychotic disorders, such as schizophrenia, schizoaffective disorder and acute polymorphic psychotic disorder (according to ICD-10), as well as the psychopathological development (Clinical Global Impression, CGI). As a secondary outcome we want to assess the overall psychopathological condition of the patients. This includes standardized and validated questionnaires comprising the clinician's impression of the patients general psychosocial functioning (Global Assessment of Functioning, GAF), suicidal symptoms (Depressive Symptom Index—Suicidality Subscale, DSI-SS) and suicidality (Suicidal Scale of the Mini-International) as well as electronic health records (EHR) of the patient's psychopharmacological medication. Generally, the standardized text of the patient's EHR will be accessible for the text-based analysis. These will be supplemented by the standardized assessment through a clinician, which will be used as the gold standard for comparison with the AI analysis.

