	Suicidality Scale of the Depressive Symptom Index (DSI-SS)	Measuring instrument for recording suicidality	
	Beck*’*s Depression Inventory (BDI- II)	Severity detection	
	Brief Psychiatric Rating Scale (BRPS)	Severity detection	
	Additional information obtained from medical record	Text based analysis	
	Medical history		
	Concomitant Medication		
Recording of the therapy sessions		Analysis of speech features	

Additionally, data on general psychosocial functioning and the severity of the patient's psychopathological state are collected using questionnaires completed by both therapists and patients.

The Clinical Global Impression (CGI) is a short assessment of the clinician's view of the patient's global functioning and to track patient progress or treatment response over time and comprises three measures of which we use two: severity of illness, global improvement, and an efficacy index (which we leave out) (48). The instrument has been proven to be a readily understood and practical measurement tool which is well applicable in the clinical practice (49) and has been used in different mental disorders including affective and psychotic disorders (50, 51). Additionally, we use the CGI-SS which is a modified version of the CGI to evaluate severity of and change in suicidality according to the version of Meltzer et al. (52). We only changed the time period from “past 7 days” to “since the last assessment”.

The Global Assessment of Functioning (GAF) scale is an established instrument for measuring illness severity in the clinical context and introduced as a rating scale within the DSM-III-R (53). The instrument has shown to be a valid and reliable measure of psychiatric illness (54).

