For each model size, we will systematically evaluate two distinct inference configurations defined by the temperature hyperparameter, which controls the randomness of model outputs. We will test a conservative configuration (temperature = 0.1) designed to prioritize consistency and clinical reliability by producing more deterministic responses, and a rather liberal configuration (temperature = 0.8). In the NLP literature the effects of temperature are well represented but systematic clinical applications have yet to be done to our knowledge. Accuracy in multiple choice question answering tasks show high consistency in temperature ranging between 0 and 1, but an expansion to other problem types is recommended (59). This strategic selection of hyperparameters reflects the clinical tension between reproducibility critical for diagnostic applications where consistency across assessments is paramount and the risk of highly inconsistent outcomes that could potentially lead to incorrect diagnoses and treatment recommendations. In addition, we apply top-p (nucleus) sampling with a cumulative probability threshold of 0.9 to each analysis. This setting restricts sampling to the smallest set of tokens whose cumulative probability mass is at least 0.9, balancing output diversity with coherence.

This yields a 2 × 2 factorial design with four experimental conditions: 1. GPT-OSS-120B with temperature 0.1, 2. GPT-OSS-120B with temperature 0.8, 3. GPT-OSS-20B with temperature 0.1, and 4. GPT-OSS-20B with temperature 0.8. We will evaluate each condition's performance on primary outcomes including general diagnostic classification accuracy and suicidality detection, severity score prediction (correlation with standardized clinical measures), and clinical utility metrics such as sensitivity, specificity, and positive/negative predictive values. All model versions, hyperparameters, and inference code will be fully documented and made available to ensure complete reproducibility.

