Concurrent with text-based analysis using GPT-OSS models, we will extract acoustic features from therapy session recordings using openSMILE (version 3.0) (56) with the eGeMAPSv02 feature set (60), which includes validated markers known to associate with psychiatric conditions. The eGeMAPSv02 feature set comprises 88 acoustic features encompassing spectral (Mel-frequency cepstral coefficients), glottal (fundamental frequency, jitter, shimmer), and prosodic characteristics (energy, speech rate, voice quality measures such as harmonics-to-noise ratio). These features will be extracted at the frame-level (10-millisecond intervals) and subsequently aggregated using statistical functions (mean, standard deviation, minimum, maximum, percentiles) to produce session-level representations comparable to clinical assessment timeframes.

Our overarching analytical strategy employs a three-tier statistical framework designed to characterize how textual, acoustic, and combined modalities contribute to clinical prediction:

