What accuracy should be expected from an AI-based suicide evaluation? Large language models demonstrate strong performance in detecting depression and suicide risk from clinical narratives, with recent real-world validation substantially informing expectations for psychotherapy transcripts. In a recent cross-sectional study of 100 admission notes from a psychiatric hospital, a German-fine-tuned Llama-2 model achieved 87.5% accuracy, 83.0% sensitivity, and 91.8% specificity in identifying suicidality status against expert ground truth, demonstrating robust performance across varied prompting strategies while preserving data privacy (64). To contextualize these capabilities, human interrater reliability in assessing mental health from dialogue provides an essential benchmark. Unstructured suicide risk assessment shows substantially lower concordance: psychotherapists demonstrate Gwet's AC₁ = 0.44 with only 58% identical risk classifications, while psychology students achieve AC₁ = 0.35 (65). Unstructured psychiatric diagnosis using clinical interviews yields *κ* = 0.24–0.43 (fair at best), compared to *κ* = 0.75 (substantial) when structured protocols guide assessment (66). This empirical gap is instructive: current clinical practice relies on unstructured judgment with relatively poor reliability, particularly for suicide risk estimation. Consequently, LLM-assisted assessment of suicidality in psychotherapy transcripts is already useful potentially when achieving only modest accuracy performance.

The dialogic nature of therapy sessions introduces complexities in transcription and analysis. Colloquialisms, pauses, overlapping speech, and non-verbal cues are integral to therapeutic communication but challenging to capture and analyze (67). Our multimodal approach aims to address these challenges by incorporating advanced speech recognition and sentiment analysis techniques. However, the nuances of therapeutic dialogue may still pose difficulties in accurate interpretation, necessitating ongoing refinement of our multimodal models.

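### The protocol assigns medical-record text to the text-based analysis but elsewhere describes only transcripts as input; as written, diagnosis could be read from the record instead of inferred from speech

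*Protocol article*

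**What the plan says.** Two places assign record text to the text analysis. Objectives says of the standardized record text that the patient's "EHR will be accessible for the text-based analysis". Table 2, in the section on assessment and collection of outcomes, has a row "Additional information obtained from medical record" whose stated purpose is text-based analysis. The rows after it are medical history and concomitant medication.

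The statistical section shows what that analysis is. It introduces the acoustic work with "Concurrent with text-based analysis using GPT-OSS models", so the term denotes the language-model arm. The four model-by-temperature conditions in that arm are judged on "primary outcomes including general diagnostic classification accuracy and suicidality detection".

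Other places describe a narrower input. Data management and the text around Figure 1 have recordings transcribed, checked and pseudonymised, after which the transcripts go to locally run language models. The Discussion says that speech data are what the prediction draws on. Objectives itself sets the aim: "Our goal is to help identify non-explicit content language patterns in clinical patients".

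**The concern.** The study is meant to show what can be inferred from how patients speak. With zero-shot prompting, whatever is placed in the prompt is the predictor. If the prompt may hold record text, the model can be given information about the target that does not come from the session.

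Three results depend on this:

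- **Diagnostic classification.** Accuracy would be largely circular if the record states the diagnosis or lists medication that points to it.
- **Comparison of modalities.** Tier 1 sets unimodal baselines, and Tier 3 measures fusion against the best of them. A text arm helped by the record is not a measure of language, and the fusion gain would be judged against a contaminated baseline.
- **Comparison with treating physicians (Outcomes).** If the record reflects those physicians' judgement, agreement between them and the model would be inflated.

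**Working it through.** The plan gives no figure for this point, and the sample size of 162 does not depend on it. The check is therefore a reading of the passages against each other.

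**1. Is record text admitted?** Yes, in Objectives and in Table 2. In the table as available, the purpose cell stands beside the medical-record row only. The cells beside medical history and concomitant medication are empty, perhaps because a merged cell was lost. Objectives does, however, name record-derived medication data separately, among the secondary-outcome material.

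**2. Is it tied to the scored arm?** Yes, by the shared term: the statistical section applies it to the GPT-OSS models, which are scored on the primary outcomes.

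**3. Is it excluded or masked anywhere?** No. Data management and the statistical section mention recordings and transcripts without ruling out record text. Pseudonymisation, under Confidentiality, is described as removing identifying details. Removal of diagnosis, medication or suicidality entries is not mentioned.

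**4. What is each target's reference?**

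| Target | Reference in the protocol | What record text could add |
|---|---|---|
| Diagnosis | The audio-based gold standard (BPRS, CGI-SS severity item, VTAS-R short form) contains no diagnosis. The only evident reference is the clinical ICD-10 diagnosis used for eligibility and collected at t1 (Table 1). | The label itself if the record states it, or a strong pointer through medication |
| Suicidality | Independent psychiatrist's CGI-SS rating made from the audio | Correlated information from outside the session, not the rating |

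Up to five sessions are recorded per patient, at least a week apart, so a record entry need not match the rating of a given session.

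**5. Size.** The protocol does not say how often the accessible record text discloses a label, so the bias cannot be computed. As an illustration for diagnosis only, assume that the record discloses the label in a share f of sessions, that the model is then always right, and that its accuracy from speech alone is a in the remaining sessions. Then

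apparent accuracy = f + (1 − f) × a.

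| a (assumed) | f = 0.25 | f = 0.50 | f = 0.75 |
|---|---|---|---|
| 0.60 | 0.70 | 0.80 | 0.90 |
| 0.70 | 0.775 | 0.85 | 0.925 |
| 0.80 | 0.85 | 0.90 | 0.95 |

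For example, 0.50 + 0.50 × 0.70 = 0.85. Neither a nor f is in the document. The table shows how the mechanism works and does not estimate this study's bias.

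**The case against.** The best defence is that the operative passages all point to transcripts. The workflow sends transcripts to the language models, the mixed models have a session-level structure, and the Discussion speaks of prediction from speech. The sentence in Objectives speaks of access, not of a specified predictor, and follows a list of secondary-outcome data. Exact prompt content is also something a condensed article may leave to a fuller document.

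Much of this stands. It shows that use of record text is permitted and not confirmed, and that transcript-only input may well be what is intended. It does not remove the conflict: Table 2 states a purpose, not mere access, and the same term names the scored arm. The point corrects a stated data use; it does not ask for missing detail.

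A reader might infer more than the document supports:

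- **That the suicidality target itself leaks.** Its reference is rated from the audio, so the record could supply only related information. That the accessible text documents suicidality, or holds the treating clinician's notes, is a reasonable inference that the protocol does not state.
- **That the expected accuracy could be reached without the recordings.** The Discussion cites 87.5% accuracy for suicidality status in a "cross-sectional study of 100 admission notes from a psychiatric hospital", close to the 89.2% in the sample-size section. The first figure has a different model, sample and reference standard, and the second is an average over prior studies used to set an effect size. Their closeness does not measure bias here.
- **That diagnostic accuracy would approach 100%.** This would need the diagnosis to be present in nearly every prompt, which is not stated.
- **That nothing could be concluded.** The acoustic-only analysis uses no text and would be unaffected.

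**Conclusion.** The point holds as an unresolved contradiction about the model input, with a material consequence if it is resolved the wrong way. Read as written, Objectives and Table 2 allow record text into the arm scored on the primary outcomes, with no exclusion or masking. If that happens, diagnostic accuracy is largely circular, suicidality detection is helped by correlated information from outside the session, and differences between text, acoustic and fused performance cannot be attributed to language.

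This rests on two assumptions: that record text would actually enter the prompts, and that it contains the diagnosis or medication indicative of it. The direction of the effect on diagnostic accuracy would be upward; its size is unknown. The change should be made before analysis, because it settles what the primary results mean.

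**What to change.** Reconcile the passages as follows:

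1. In the statistical section, state that the text input for the primary outcomes and for the fusion comparison is the pseudonymised session transcript only.
2. If record text is to be used, report that run as a separate, labelled secondary analysis outside the fusion comparison. Mask diagnosis entries and, for diagnostic classification, medication as well.
3. In Table 2, change the purpose of the medical-record information to match (for example sample description, reference diagnosis and secondary analysis), and align the sentence in Objectives.

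The cost is about one sentence in the statistical section, a matching edit in Objectives and one table cell. No additional data are needed, and use of the record is kept. The downside is that reported accuracy may be lower than with record text in the prompt.

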## Trial design

The study is multicentric, data will be collected via the University hospital in Frankfurt and in the Private Clinic [name] in Königstein and will be processed by data scientists from the TU Darmstadt. The raw data will be stored exclusively on protected local servers at the University hospital Frankfurt and only pseudonymized data will be transferred to Darmstadt.

## Methods: participants, interventions and outcomes

### Study setting

Data will be collected in the University hospital in Frankfurt a.M. Additionally, one clinician and project member will collect data at the private hospital [name] in Königstein. Data access is regulated via a data security protocol.

### Eligibility criteria

We will include patients with ICD-10 diagnoses F20.x, F23, F25, F30-33, aged between 18 and 65 years, who are legally competent, without any issues in voice production, and have a German speaking proficiency of at least B2 (lower level in German would contain too little information content of linguistic utterances). Additionally, psychotherapists employed at the University Hospital Frankfurt will be included for the therapeutic conversations.

### Who will take informed consent?

Informed consent will be contained by members of the study team who are not involved in the patients care. The patients are addressed at least one day prior to study participation and informed about the study. One day later, they will be addressed again and sign the consent if interested in participation.

## Interventions

### Explanation for the choice of comparators

n/a: No comparator treatment was conducted. All participants equally engaged in receiving therapy sessions and completing questionnaires.

### Intervention description

The participation will consist of the recordings of the therapeutic clinical conversations that are carried out in the regular clinical practice. In addition, for our study a student assistant will place a recorder and microphones before the therapy session and pick it up afterwards. This student assistant will be absent during the therapy session and only install the recording hardware. Further, after the recorded therapy session the clinicians and participants are required to fill out questionnaires regarding the clinical state and suicide risk of the patient on the same day as the therapy session was recorded.

### Criteria for discontinuing or modifying allocated interventions

Study participation will be discontinued if the patients or their therapist request to discontinue participation or if the patient's clinical treatment is completed.

### Strategies to improve adherence to interventions

To maintain adherence as much as possible, we strive to integrate the participation process seamlessly into the clinical routine of both patients and therapists. The only additional effort required for participation is approximately 5 min to fill out questionnaires after a recorded therapy session.

### Provisions for post-trial care

n/a: we do not expect that patients suffer any harm from participation, since the recordings are conducted as part of their regular therapeutic care and participants additionally only fill out questionnaires.

### Outcomes

As part of an initial exploratory analysis, the assessment of psychopathology by treating physicians is to be compared with the evaluation by a computer model. Therefore, using intraclass correlation coefficients or t- tests, the hypothesis “There is no difference in the assessment of patients regarding the severity of illness and suicidality” will be tested.

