### Sample size

To determine the required sample size for comparing the accuracy of our models against the gold standard of a trained psychiatrist's evaluation, we conducted an *a priori* power analysis using G*Power software (43).

We based our effect size estimate on the accuracies reported in previous studies that used machine learning techniques to predict suicidality from clinical data (44). Pestian et al. (45) reported an accuracy of 85%, Bernert et al. (46) reported 90% among 87 studies in their meta-analysis, and Barak-Corren et al. (47) reported 94%. The average accuracy across these studies is 89.2%. Assuming a gold standard accuracy of 100%, we calculated an effect size (Cohen's g) of 0.11 using the formula: g = (P—Po)/√[Po(1—Po)], where *P* is the expected accuracy (0.892) and Po is the gold standard accuracy (1.0).

For our power analysis, we set the following parameters: a two-tailed test, an alpha level of 0.05, a power of 0.80, and a constant proportion of 0.5 (representing a balanced dataset). The results indicated that a total sample size of 162 is required to detect an effect size of 0.11 with 80% power at a significance level of 0.05. The critical values for the lower and upper bounds of the acceptance region are 68 and 94, respectively. The actual power achieved with this sample size is 0.8046757, and the actual alpha level is 0.0491726.

In summary, to compare the accuracy of our models against the gold standard of a trained psychiatrist's evaluation with 80% power and a 5% significance level, we require a total sample size of *n* = 162, assuming an effect size of 0.11 based on the accuracies reported in previous comparable studies. As we expect a drop-out rate of 15%–20% due to technical issues, quality issues etc., we expect to collect *n* = 200 interviews.

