
## Statistical methods

### Statistical methods for primary and secondary outcomes

We will employ a zero-shot prompting approach with OpenAI's recently released GPT-OSS (Generative Pretrained Transformer—Open Source Software) series models, which are available under the permissive Apache 2.0 license and have demonstrated strong performance on reasoning tasks relevant to clinical assessment. We have selected these models for several methodological and practical reasons:

First, their open-weight nature ensures full transparency and reproducibility of our analyses. Second, their mixture-of-experts architecture enables efficient deployment on clinical infrastructure with limited computational resources. Third, their documented performance on complex reasoning tasks, including healthcare-related queries, makes them well-suited for psychiatric assessment applications.

Our primary analytical comparison will involve two model sizes from the GPT-OSS family: GPT-OSS-120B (116.8 billion total parameters with 5.1 billion active parameters per token) and GPT-OSS-20B (20.9 billion total parameters with 3.6 billion active parameters per token) (58). This comparison directly addresses a critical question for clinical deployment: whether larger, more capable models provide sufficient performance advantages to justify their greater computational demands, or whether smaller, more efficient models can achieve comparable diagnostic accuracy. The GPT-OSS-120B model has been shown to achieve near-parity with state-of-the-art reasoning models on standard benchmarks while running efficiently on a single 80GB GPU, whereas GPT-OSS-20B delivers comparable performance to advanced compact models while requiring only 16GB of memory, making it feasible for deployment on standard clinical workstations or even edge devices.

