Tier 1: Unimodal Baseline Analysis. We will analyze each modality independently to establish baseline predictive performance before considering fusion. For the text modality, we will conduct two-way mixed-effects logistic regression with outcomes (diagnostic classification or severity degree) regressed on the fixed effects of model size and temperature, with random intercepts for participant and session. Effect sizes will be reported as odds ratios with 95% confidence intervals. For the acoustic modality, we will conduct mixed-effects linear regression using a reduced set of the most clinically relevant acoustic features selected *a priori* based on prior literature associations with depression and suicidality, including pitch variability, energy measures, MFCC and jitter as predictors of continuously scored clinical outcomes (e.g., severity scores from standardized rating scales) (60, 61).Tier 2: Factorial Interaction Analysis for 2 × 2 Design. For text-based predictions, we will formally test the 2 × 2 factorial design using mixed-effects ANOVA to partition variance according to main effects (model size, temperature) and their interaction. Specifically, we will model primary outcome (e.g., predicted depression severity) as a function of fixed effects for model size (GPT-OSS-120B vs. 20B), temperature (0.1 vs. 0.8), and their interaction (Model Size × Temperature), with random intercepts for participants and sessions to account for the hierarchical data structure. This approach allows us to determine whether inference strategy recommendations (conservative vs. liberal temperature) can be applied consistently across model sizes, or whether optimization differs by model choice. If a significant Model Size × Temperature interaction emerges, it would suggest that clinical deployment requires model-specific tuning. Conversely, absence of interaction would support unified recommendations applicable regardless of computational constraints. We will report partial eta-squared (*η*²p) effect sizes with 95% confidence intervals for each factorial term.Tier 3: Multimodal fusion and Late-Fusion Integration. To evaluate how textual and acoustic information combine for clinical prediction, we will employ a structured late-fusion approach. For each of the four 2 × 2 factorial conditions, we will generate separate predictions from the GPT-OSS models (text modality) and from a logistic regression model trained on acoustic features (acoustic modality). We will then integrate these predictions through weighted averaging, with weights determined via cross-validation (80% training, 20% held-out validation) on a stratified subset of sessions. This approach maintains interpretability—each modality's contribution can be quantified—and avoids the architectural complexity that would introduce uncontrolled hyperparameter flexibility incompatible with pre-registration.We will quantify multimodal benefit by comparing fusion performance (AUC, sensitivity/specificity at clinically relevant decision thresholds) against the best unimodal baseline. If fusion provides incremental improvement beyond single modalities, we will use mixed-effects logistic regression with interaction terms to test whether the fusion benefit depends on model size or temperature setting. This tests the hypothesis that acoustic information provides complementary information that enhances text-based predictions uniformly, or whether certain model configurations better leverage multimodal information.

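### The clinician-versus-model comparison allows a t-test where agreement is the question, and the factorial analysis draws a recommendation from a null interaction

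*Protocol article*

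**What the plan says.** The Outcomes section sets up the comparison of clinician and model: "As part of an initial exploratory analysis, the assessment of psychopathology by treating physicians is to be compared with the evaluation by a computer model". It names the methods and the target in one clause, "using intraclass correlation coefficients or t- tests, the hypothesis", followed by the hypothesis itself: "There is no difference in the assessment of patients regarding the severity of illness and suicidality". It gives no rule for choosing between the two methods.

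In the section on statistical methods for primary and secondary outcomes, Tier 2 fits a model with model size, temperature and their interaction. A significant interaction is to be read as a need for model-specific tuning. The other outcome is also given a meaning: "Conversely, absence of interaction would support unified recommendations applicable regardless of computational constraints". The same tier plans partial eta-squared with a 95% confidence interval for every factorial term, and the fixed effects are tested at a two-sided 0.05 level.

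The Sample size section describes "a two-tailed test, an alpha level of 0.05, a power of 0.80, and a constant proportion of 0.5" and concludes that "a total sample size of 162 is required to detect an effect size of 0.11".

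**The concern.** The question is whether the model rates the same patient as the clinician does. A t-test answers a different one: whether the two sets of ratings have the same average. Scores can share a mean and be unrelated patient by patient, or track each other closely with a small constant offset. The t-test tends to favour the first case over the second.

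The two options also point in opposite directions. With a t-test of no difference, a significant result counts against the model. With the usual F-test of an ICC against zero, a significant result counts for it. Leaving the choice open lets the same data support either conclusion. It also sits badly with the article's claim, at the end of the statistical methods, that the plan rules out methodological choices made after the fact.

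The Tier 2 sentence has a related fault. It attaches a deployment recommendation to a null result, and the less precise the data, the more often a null result occurs. Suicide risk assessment is part of the primary aim, so a mistaken claim of agreement or of interchangeable settings would matter.

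**Working it through.** **1. The plan's own figure.** Inputs from the Sample size section: null proportion 0.50, effect size 0.11, two-sided alpha 0.05, power 0.80. Read as an exact one-sample binomial test with p0 = 0.50 and p1 = 0.50 + 0.11 = 0.61, at most 0.025 in each tail, n = 162 gives critical values 68 and 94, actual alpha 0.04917 and power 0.80468. This matches the article: "The critical values for the lower and upper bounds of the acceptance region are 68 and 94, respectively". Dropout inflation gives 162/0.85 = 190.6, so 191, and 162/0.80 = 202.5, so 203, consistent with about 200 interviews. The calculation reproduces, but it is sized to tell a proportion of 0.61 from 0.50. It covers neither agreement nor an interaction.

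**2. The t-test route.** Assumptions, since the article gives no score SD, mean shift or correlation: unit-SD normal scores, independent pairs, a paired t-test. With correlation ρ and mean shift δ (in SD), the difference has SD √(2(1 − ρ)) and the test has noncentrality δ√n / √(2(1 − ρ)).

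- Unrelated model, ρ = 0, δ = 0.2, n = 162: 0.2 × 12.73 / 1.414 = 1.80. P(non-significant) ≈ Φ(1.96 − 1.80) = Φ(0.16) ≈ 0.56.
- Good model, ρ = 0.9, δ = 0.1, n = 162: 0.1 × 12.73 / 0.447 = 2.85. P(non-significant) ≈ Φ(1.96 − 2.85) = Φ(−0.89) ≈ 0.19.

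Simulation with 4,000 replicates per setting agrees. Share of studies with p > 0.05:

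| Model | Shift (SD) | n = 162 | n = 200 | Mean ICC |
|---|---|---|---|---|
| Unrelated (ρ = 0) | 0 | 95% | 95% | about 0 |
| Unrelated | 0.1 | 85% | 84% | about 0 |
| Unrelated | 0.2 | 56% | 49% | about 0 |
| Unrelated | 0.3 | 24% | 15% | about 0 |
| Unrelated | 0.5 | 0.6% | 0.2% | about 0 |
| Good (ρ = 0.9) | 0.1 | 19% | 11% | 0.89 |

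**3. The ICC route.** For the unrelated model the F-test of the ICC against zero is significant in only about 5% of studies, whatever the shift. For the good model the absolute-agreement ICC is 0.9 / (1 + 0.1²/2) = 0.896, against a simulated mean of 0.894, and the F-test is significant in essentially every study. The ICC separates the two models; the t-test can order them the wrong way round.

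**4. The interaction.** As an illustration only, assume an accuracy outcome with 85% in each cell, 162 sessions, correlation r between cells within a session, and no patient clustering. The interaction contrast has variance 4 × 0.85 × 0.15 × (1 − r)/162 = 0.00315(1 − r). At r = 0 the standard error is 0.056 and the effect detectable with 80% power is 2.80 × 0.056 = 0.157, about 16 accuracy points. At r = 0.8 it is 2.80 × 0.0251 = 0.070, about 7 points. Interactions of that order could be missed and then read as absent.

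**The case against.** The strongest reply is that a reader might infer more than the article supports. Five such points are fair.

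- A reader might infer that p > 0.05 will be declared agreement. The Outcomes section says only that the hypothesis will be tested. Non-rejection is the only t-test result that could favour the model, but that reading is inferred; the reading of a null result is explicit only in Tier 2.
- A reader might infer that an unrelated model would usually be found no different. That needs the t-test option and means within about 0.2 SD. Nothing shows that a zero-shot model would match the clinician's mean, and the ICC, which the article names first, would expose an unrelated model.
- The comparison is labelled exploratory. The statistical methods list classification accuracy, correlation with clinical measures, sensitivity, specificity and predictive values as primary outcomes, and Tier 3 adds AUC. An unrelated model would do badly on these.
- A reader might see the same fault in the question "whether smaller, more efficient models can achieve comparable diagnostic accuracy". That phrase motivates the model comparison; no test or inference from non-significance is attached to it.
- An interval for the interaction is already planned, so it is not missing.

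These points narrow the problem without removing it. The article itself permits an unsuitable test, so this is not detail left to an analysis plan. The other accuracy measures do not repair that comparison, and the planned interaction interval is not tied to the Tier 2 conclusion.

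**Conclusion.** The point holds in a limited form. In the Outcomes section the fault is the t-test option and the unresolved choice between it and the ICC. At n = 162, an unrelated model with an equal mean is non-significant in about 95% of studies, against about 19% for a model with correlation 0.9 and a 0.1 SD shift. The unrelated model's share falls to 56% at 0.2 SD and under 1% at 0.5 SD.

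In Tier 2 the fault is one sentence that draws a positive conclusion from a null result, in a study whose sample size was not set for that purpose.

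The percentages rest on assumed shifts and correlations, normal scores and a paired test. They also treat pairs as independent although up to five sessions per patient are recorded, so clustering would alter them. The statement that a t-test does not measure agreement depends on none of these.

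**What to change.** **Outcomes section.** Remove the t-test as evidence of agreement. Use the absolute-agreement ICC, with weighted kappa for the five-stage CGI-SS severity item, each with a 95% confidence interval that allows for several sessions per participant. Claim agreement only if the lower limit exceeds a minimum stated in advance. Show mean bias and limits of agreement as description only. A margin on the mean difference alone would not do, because an unrelated model with the same mean could meet it.

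**Tier 2.** Base any advice common to both model sizes on the interaction confidence interval already planned, compared with a stated margin. State that a non-significant interaction will not be read as absence.

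**Cost.** Wording, plus the choice of a minimum and a margin; no new data. Some comparisons may end as inconclusive. By Fisher's z with variance 1/(n − 1.5), an ICC of 0.75 has an interval of about 0.67 to 0.81 with 162 independent pairs, and about 0.58 to 0.86 with 40 independent units (200 interviews at five per patient, the worst case). The minimum should be chosen with that precision in view.
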